To improve adherence, participants are enabled to write an action plan at the end of each appointment. Progress in meeting the plan is reviewed at the beginning of the next appointment. The plan and progress are recorded in the WES-RC continuation notes. The participant is reminded about any elements still to be completed or ongoing. If a participant does not attend or respond to the therapists attempts to re-schedule the appointment (four attempts can be made by telephone and in writing), the therapist will record this and reason for non-attendance (if known) in the Treatment Record. In the feasibility trial 25/29 intervention group participants attended [25]. We therefore anticipate an 86% adherence rate with attending WORKWELL although it could be lower.

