### Concomitant care

Therapists are asked not to provide work rehabilitation to control group participants whilst they are in the trial (i.e. during their one-year participation). All participants continue to receive usual care, i.e. Rheumatology clinic appointments, prescribed medication and referrals to the multidisciplinary team, as applicable, for rehabilitation. Data on participants’ use of concomitant care is collected via the baseline, six- and 12-month questionnaires.

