### Criteria for discontinuing or modifying allocated interventions

The WORKWELL intervention will be delivered by the WORKWELL Therapist to meet the participant’s individual needs, selecting from the range of solutions available. WORKWELL will be discontinued only if: the treating therapist identifies a serious adverse event resulting from WORKWELL; or the participant stops attending. Serious adverse events resulting from WORKWELL are not expected due to the low risk associated with the intervention; none were identified in the feasibility study. If treatment stops, the date and reason will be recorded by the therapist. It is highly unlikely any harm will arise from receiving the work self-help information pack. Any participant discontinuing WORKWELL will remain in the trial for follow-up unless choosing to withdraw.

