### Sample size

This was calculated using data from the feasibility study. The minimal clinically important difference for the WLQ-25 is estimated as 13 points in the summed score [57]. The standard deviation (SD), pooled across the intervention and control groups, was 20.64 in the feasibility trial. As the SD might be an under-estimate, the 80% upper one-sided confidence limit of the estimated SD, i.e. 23.02, was used. Although the WORKWELL trial is individually, rather than cluster randomised, we are concerned that the effect of the WORKWELL intervention may vary by therapist (as there is more than one therapist at 11 of the 22 hospitals in the 18 sites). This could lead to a clustering effect on outcome. No such effect is expected in the control intervention. We therefore performed the sample size calculation using the *clsampsi* Stata command [58]. As we do not expect the clustering effect to be large, the intra-class coefficient (ICC) for the WORKWELL intervention arm = 0.05 and control arm = 0. To identify a 13-point difference, SD = 23.02, *p* = 0.05 and 90% power, 90 participants are required in each group. Allowing for a 25% attrition rate at 12 months (i.e. non-completion of the WLQ-25 at 12 months due to no longer working or on long-term sick leave; or non-return of the 12-month questionnaire) we intend to recruit and randomise 240 participants in equal numbers to the two groups. We anticipate we may need to obtain consent from up to 300 patients to achieve 240 participants at randomisation (as some will not complete and return their baseline questionnaire, and some may become ineligible prior to randomisation) and 180 participants with 12-month outcome data.

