### Statistical methods

Primary effectiveness analyses will follow a pre-specified Statistical Analysis Plan (approved by the Trial Steering Committee (TSC) and available on request) and will include the intention to treat population. Data will be summarised using means, medians or proportions as applicable. The primary analysis will use mixed effects linear regression to estimate the effect of group allocation on WLQ-25 summed index scores, controlling for the stratification variable in the randomisation process (skill level group) and the baseline value of the WLQ-25 (both fixed effects) and therapist (random effect); the six- month and 12-month outcomes will be analysed in a single model with an interaction term between time point (six or 12 months) and randomised group to determine the treatment effect at both time points separately. Secondary effectiveness analysis will repeat the primary analysis method for all other outcomes, using appropriate generalised linear mixed modelling methods (i.e. mixed effects linear, logistic or ordinal logistic regression) including six- and 12-month outcomes as available, controlling for the stratification variable, baseline value of the specific measure and therapist effect. The interaction between time point and randomised group will not be included for outcomes measured only at 12 months. Sensitivity analyses will include the analysis of the primary outcome measure excluding anyone allocated to the intervention who did not attend WORKWELL and anyone allocated to control but did receive WORKWELL (the per protocol population). We do not anticipate undertaking sensitivity analyses on the basis of missing data unless there is a great deal and/or large imbalance in missingness between the two trial groups.

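### The per-protocol sensitivity analysis compares self-selected WORKWELL attenders with nearly all controls and is open to selection bias; a complier-average estimate with stated assumptions should be added and preferred for the effect of attending.

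*Protocol article*

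**What the plan says.** Under Statistical methods, the primary effectiveness analyses "will include the intention to treat population". In an open-ended list of sensitivity analyses, the same section names one for the WLQ-25, formed by "excluding anyone allocated to the intervention who did not attend WORKWELL and anyone allocated to control but did receive WORKWELL", and calls what remains the per-protocol population. Sensitivity analyses for missing data are not expected unless missingness is extensive or unbalanced, so this is the only sensitivity analysis to which the article firmly commits.

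On attendance, the section on the WORKWELL intervention group reports "In the feasibility trial 25/29 intervention group participants attended". From this the article draws its expectation for the present trial: "We therefore anticipate an 86% adherence rate with attending WORKWELL although it could be lower".

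Two other statements matter. On stopping the intervention: "Any participant discontinuing WORKWELL will remain in the trial for follow-up unless choosing to withdraw". On control access, under Concomitant care: "Therapists are asked not to provide work rehabilitation to control group participants whilst they are in the trial".

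**The concern.** Attendance is observed after randomisation, and in practice only in the arm that is offered appointments. Removing non-attenders from that arm leaves people willing and able to attend. The control arm keeps both kinds of people, because nobody can tell which controls would have stayed away. Dropping controls who received WORKWELL is a second post-randomisation selection, probably a small one.

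The contrast is biased if would-be non-attenders have a different outlook on presenteeism from attenders. The article has no data on this, but it makes a link plausible. Appointments are placed early or late in the day to fit around work, the Recruitment section foresees patients who cannot stay in clinic because of work, and the WLQ-25 includes subscales for time and output demands. Work pressure could therefore affect both attendance and outcome.

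What is at stake is interpretation. The per-protocol and intention-to-treat estimates target different quantities, so agreement does not show robustness and disagreement does not show fragility. A reader could also take the per-protocol figure as the effect of receiving WORKWELL when part of it may be selection.

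**Working it through.** **Inputs from the protocol article.** Feasibility attendance is 25 of 29 (WORKWELL intervention group). The minimal clinically important difference is 13 points and the SD is 23.02, with 90 per group analysed (Sample size).

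**Assumptions.** Control uptake of WORKWELL is taken as zero; the article discourages it but gives no rate. The prognostic gap d is the mean WLQ-25 of would-be non-attenders minus that of would-be attenders, both without WORKWELL. The article gives no value, so a range is used. A higher WLQ-25 score means more limitation, so a beneficial effect is negative.

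**The plan's own figure.** 25/29 = 0.862, which agrees with the stated 86%. Non-attendance is 4/29 = 0.138.

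**Derivation.** Let c be attendance, τ the effect in attenders, and μ the attenders' mean without WORKWELL. Suppose allocation does nothing for non-attenders.

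- Control mean: μ + (1 − c)d.
- Mean of attenders in the intervention arm: μ + τ.
- Per-protocol contrast: τ − (1 − c)d, so its bias for τ is −(1 − c)d.
- Intention-to-treat contrast: cτ, so τ = ITT/c, the complier-average effect.

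**Size of the per-protocol bias (absolute value).**

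| Assumed gap d | c = 0.862 | c = 0.70 (assumed) |
|---|---|---|
| 5 points | 0.138 × 5 = 0.7 | 0.30 × 5 = 1.5 |
| 10 points | 0.138 × 10 = 1.4 | 0.30 × 10 = 3.0 |
| 15 points | 0.138 × 15 = 2.1 | 0.30 × 15 = 4.5 |

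At 86% attendance this is 5% to 16% of 13 points (0.69/13 and 2.07/13). With d = 0 the bias is zero. If non-attenders would score worse, the per-protocol result exaggerates the benefit; if better, it understates it. If these are raw gaps, the figures are upper values, because adjustment for baseline WLQ-25 and skill level would normally shrink them.

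**Different targets even without selection.** With d = 0 and τ = 13 points in size, the per-protocol contrast is 13 and the intention-to-treat contrast is 13 × 0.862 = 11.2. Conversely, an intention-to-treat effect of 13 corresponds to 13/0.862 = 15.1 in attenders.

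**Simulation.** 4,000 runs, 90 per arm, SD 23.02, c = 25/29, gap of half an SD (11.51 points), without baseline adjustment or clustering:

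| True effect in attenders | ITT | Per-protocol (empirical SE) | Complier-average (empirical SE) |
|---|---|---|---|
| 0 | −0.01 | −1.60 (3.63) | 0.02 (4.07) |
| −13 | −11.23 | −14.61 (3.53) | −13.00 (3.97) |

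**When the complier-average estimate fails.** If allocation changes non-attenders' scores by e points, its bias is e(1 − c)/c = e × 4/25. For e of 2 and 5 points this is 0.32 and 0.80 points.

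**The case against.** The strongest reply is that this is a supporting analysis beside an intention-to-treat primary, clearly defined, and no conclusion in the article depends on it. That stands, and it limits the weight of the point.

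The size is also hypothetical. No gap is given, reasons for non-attendance are only to be recorded where known, and ability to attend appointments is an entry criterion in both arms. If the primary model is reused, only the gap left after adjustment for baseline WLQ-25 and skill level matters. The biases at 86% attendance are below the simulated standard error of about 3.5. All of this stands. It makes the bias modest and uncertain but does not restore the randomised comparison.

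The complier-average estimate is not free of bias either. It needs the exclusion restriction, and participants are unblinded and report their own outcomes. It needs monotonicity. It does not by itself deal with the 25% expected to lack a 12-month WLQ-25, and plain two-stage least squares ignores therapist clustering. These limits stand and belong in the plan. In its favour, both arms receive the same information pack and usual care, so a non-attender gets nearly what a control gets.

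Finally, the statistical analysis plan is not shown and the list of sensitivity analyses is open-ended, so a complier-average analysis may already be planned. Its absence from the article is therefore not the point. The point is the exclusion rule that the article does state, which a further analysis would supplement but not change.

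**Conclusion.** The point holds as a cheap improvement to a secondary analysis. The stated rule compares self-selected attenders with nearly all controls. At 86% attendance the bias is about 0.7 to 2.1 WLQ-25 points for assumed residual gaps of 5 to 15 points; at an assumed 70% it is 1.5 to 4.5. These figures rest on the assumed gaps and on negligible control uptake.

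Three stronger readings are tempting and are not supported. A reader might infer that the attenders are compared with all controls, but the rule also drops controls who received WORKWELL. A reader might infer that the trial's main conclusion is compromised, but that rests on intention to treat and is untouched. A reader might infer that the per-protocol analysis must be deleted because a complier-average estimate is unbiased. That estimate removes attendance selection only under its own assumptions, and it answers a specific question: the effect in people who would attend if offered, with attendance reduced to yes or no.

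**What to change.** Add a complier-average causal effect for the 12-month WLQ-25 and prefer it for the effect of attending. Use randomised group as the instrument for attending at least one WORKWELL session, adjust for baseline WLQ-25 and skill stratum, and include all randomised participants with outcome data. Allow for therapist clustering in the standard errors. State the exclusion restriction, monotonicity and the handling of missing outcomes. Any control uptake should enter through the observed attendance in both arms, so that the divisor is the difference in attendance and not 0.86 by assumption.

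If the per-protocol analysis is kept, report it as supplementary and open to selection bias, and do not present it as a robustness check of the intention-to-treat estimate.

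The cost is one extra model and some wording. No new data collection is needed, because those who stop WORKWELL remain in follow-up unless they withdraw. The price is a wider interval (simulated standard error about 4.0 against 3.5) and dependence on the exclusion restriction in an open-label trial with self-reported outcomes. If the analysis plan already contains such an estimate, only the labelling of the per-protocol result needs to change.

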#### Economic evaluation

A cost-effectiveness analysis (CEA) approach will be used in the economic evaluation. The base case analysis will be conducted in line with the NICE Reference Case [61]. The costs and outcomes of WORKWELL will be compared to those associated with the provision of usual care plus the information pack. Additional economic analyses will consider alternative outcomes measures and perspectives (see *E*co*nomic analysis* section below).

#### Costs

Costs to be included in the analysis will reflect those incurred by the NHS in terms of providing care in the control arm and the intervention arm along with any use of NHS services over the one-year time horizon of the CEA. Unit costs, identified from relevant sources (e.g. Department of Health reference costs), will be attached to the collated resource use data to provide overall costs for each arm of the study.

#### Outcomes

In the base case analysis, Quality-Adjusted Life Years (QALYs) will be generated for each arm of the trial using the EQ-5D-5L scores mapped onto EQ-5D-3L utility values as recommended by NICE [62]. The SF-12v2 health status measure will be used to generate QALYs in an additional CEA. Further analyses will employ the WLQ-25 and the WPAI as outcome measures for CEAs (see Economic analysis section below).

#### Economic analysis

Net costs and outcomes for each arm of the trial, adjusted for baseline characteristics, will be estimated in regression models. Using an NHS perspective in the base case CEA, an incremental cost-effectiveness ratio (ICER) will be calculated to reflect the cost per unit difference in QALYs associated with WORKWELL compared to usual care plus information pack provision. Bootstrapping – where multiple ICERs are generated through the resampling of trial data – will be used to characterise uncertainty in the combined cost and outcomes data. Cost effectiveness acceptability curves, populated with bootstrapped data, will be used to illustrate the probability that WORKWELL is cost-effective given the NICE-recommended threshold of acceptability [61].

Additional scenario analyses will comprise:
a CEA conducted in line with the base case analysis but using the SF-12 to generate QALYs; previous work has indicated that this tool is particularly appropriate for the economic evaluation of work-based interventionsa CEA in which the ICER represents the cost to employers for reduced presenteeism as measured by the WLQ-25a CEA in which the ICER represents the cost to employers for reduced presenteeism as measured by the WPAIa CEA in which the ICER represents the cost to employers for QALY gains and where levels of presenteeism, as measured by the WLQ-25, are translated into costs using the human capital approach

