### Objectives

The primary objective is to assess whether there is a clinically important difference in work presenteeism (measured using the Work Limitations Questionnaire–25: WLQ-25 [27]), in people with RA, UIA or PsA receiving: WORKWELL JRVR compared to written work self-help information, in order to assess the work-related benefits to patients.

The secondary objectives are to:
i.Assess the effectiveness of WORKWELL JRVR relative to the control intervention on: work activity limitations, work instability, work productivity, absenteeism, work status, satisfaction with work advice/support received, work self-efficacy, health status and quality of life.ii.Determine the cost-effectiveness of WORKWELL JRVR from both an NHS and employer perspective.iii.Understand the social and structural context in which the intervention is delivered and to identify factors which may influence the quality of implementation, through conducting a process evaluation.iv.Investigate contextual factors influencing participants’ presenteeism.

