**Secondary outcome measures**					
Presenteeism	Work Activities Limitations Scale^a^ (WALS) [40]	12 items: degree of difficulty in work activities (0 = no difficulty; 3 = unable to do)	✓	✓	✓
	Combined WLQ-25 WALS^a^ [41]	Combination of above two measures	✓	✓	✓
	WLQ-25 [27]	4 subscales calculated from relevant items in the WLQ-25 questionnaire	✓	✓	✓
Absenteeism and Presenteeism	Work Productivity and Activity Impairment Questionnaire General Health V2.0 (WPAI-GH) [42]	Last 7 days: time off on sick leave/any other reason; hours worked; health problems effect on work productivity and ability to do other daily activities.	✓	✓	✓
Work status	Work Transitions Index [43]	Whether employed; in full- or part-time work	✓	✓	✓
Work instability	Work instability scale (RA-WIS) [30]	23 true/false items: degree mismatch between functional abilities and workplace demands	✓		✓
Work self-efficacy		0–10-point numeric rating scales (NRS) 0 = not at all to 10 = very. 3 work self-efficacy items (confidence in working, managing health condition at work and work not making condition worse (0–10 NRS)	✓		✓

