**Contextual Factors: Personal**					
Personal appraisal	Job strain [53]	One item: stress currently experienced at work	✓		✓
	Work motivation/ importance/self-efficacy	3 items: motivation, importance and confidence to continue working (0–10 NRS) (0–10 NRS)			
	Disclosure [50]	Disclosure about condition to employer /line manager	✓		✓
	Job satisfaction	Satisfaction with job: 0–10 NRS	✓		✓
	Future job expectations	Two items: concerns about health affecting ability to work in future; and likelihood of leaving job in the next year due to arthritis	✓		✓
Work-Life Balance	Work-life balance [54].	Four items: perceived work-life balance taken from the Work, Health Life Balance Perceptions Scale	✓		✓

Notes: ^a^ the WLQ-25 and WALS will be collected within the Combined WLQ-25 WALS dual scored measure [41]

Each month, employment status and absenteeism will be collected by the Lancashire Clinical Trials Unit via e-mail or telephone

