#### Work- related outcome measures

i)The Work Limitations Questionnaire (WLQ-25): a 25-item reliable, valid measure of presenteeism, indicating the amount of time, in the last 2 weeks, a person was limited in: physical work demands, time demands, mental-interpersonal demands and output demands. The summed score (i.e. of the four sub-scales) will form the primary outcome measure [27].

Secondary outcomes include:
ii)**Presenteeism**:WLQ-25 sub-scales: the four subscales measuring physical work demands, time demands, mental interpersonal demands and output demands from specific items in the WLQ-25 questionnaire [27].The Work Activities Limitations Scale (WALS): a reliable, valid measure including 12 items assessing degree of difficulty performing work activities (0 = no difficulty; 3 = unable to do [40].

The WLQ-25 and WALS will be collected using the combined WLQ-25 and WALS, from which each can be calculated, as well as a dual-key scored outcome [41]. Subsequent to the trial starting, this dual-key scored outcome is now supported by the OMERACT Work Productivity Group as the current best available measure of presenteeism, and a better predictor of work cessation than the original WLQ-25 [41, 55].
The Work Productivity and Activity Impairment Questionnaire General Health V2.0 (WPAI:GH): a reliable, valid measure of extent of absenteeism, presenteeism, and impairment in daily activities attributable to general health [42].iii)Work status: whether in full- or part-time work at six and 12 months, collected using the Work Transitions Index [43];iv)Absenteeism**:** each month, the number of days sickness absence attributable to arthritis or other causes. This is collected by text, e-mail or telephone.v)RA-Work Instability Scale (RA-WIS): at 0 and 12 months: reliable, valid measure including 23 true/false items measuring mismatch between functional abilities and job demands [30]vi)Work Self-efficacy: at 0 and 12 months: three 0–10 numeric rating scales (NRS) asking about confidence in: ability to work; ability to manage their health condition at work; and working will not make their health worse. Additionally, three 0–10 NRS will be used to measure: motivation; importance and confidence to continue working over the next year.

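### The employer scenario that values lost production names only WLQ-25 presenteeism for costing and gives the monthly sickness-absence days no stated role

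*Protocol article*

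**What the plan says.** In the Protocol article, Objectives, secondary objective ii reads: "Determine the cost-effectiveness of WORKWELL JRVR from both an NHS and employer perspective".

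The section Economic analysis sets the NHS perspective with QALYs as the base case and then lists additional scenarios. Three of these take the employer's side. In two, presenteeism (WLQ-25 or WPAI) is the effect measure. In the third, the effect is QALYs and lost production enters as cost: "where levels of presenteeism, as measured by the WLQ-25, are translated into costs using the human capital approach".

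The section Costs describes NHS items: "Costs to be included in the analysis will reflect those incurred by the NHS". The employers' cost is not itemised there or under Economic analysis, and absence is not mentioned anywhere in the economic sections.

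Absence is nevertheless measured. Work-related outcome measures lists it as a secondary outcome: "each month, the number of days sickness absence attributable to arthritis or other causes". The note under Table 1 says: "Each month, employment status and absenteeism will be collected by the Lancashire Clinical Trials Unit via e-mail or telephone". The WPAI entry in Table 1 also covers absence ("Last 7 days: time off on sick leave/any other reason; hours worked"), but Economic analysis uses the WPAI only for presenteeism.

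The section Sample size counts as attrition "non-completion of the WLQ-25 at 12 months due to no longer working or on long-term sick leave".

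**The concern.** From an employer's side, lost production has two parts: reduced output on days worked, and days not worked at all. The one scenario that turns lost production into money names only the first. The WLQ-25 measures limitation at work over the last two weeks, so it does not capture days away. For people on long-term sick leave or no longer working, the plan expects no 12-month score, and these are the people with the largest loss.

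The intervention is meant to keep people in work, so absence is one of the places where an effect might appear. If the arms differ in absence and it is left out, the employer-cost difference will be too small or too large. The employer half of objective ii would then rest on an incomplete cost, although the trial holds the data to complete it.

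**Working it through.** The document states no employer-cost figure, so there is nothing to reproduce. The check shows what leaving absence out does to a difference between arms, in paid-day equivalents per person-year.

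**Inputs.** None of these is in the document; all are assumptions for illustration.
- W = 225 scheduled working days a year
- A = absence days: 8 in the control arm, varied in the WORKWELL arm
- p = fraction of output lost on days worked: 10% in control and 7% with WORKWELL, with other pairs below

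**Formulas.**
- Presenteeism-only cost = p × (W − A)
- Full cost = A + p × (W − A)
- Difference = WORKWELL minus control; negative means a saving

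**Worked line** (loss 10% to 7%, absence 8 to 4):
- Presenteeism only: 0.07 × 221 − 0.10 × 217 = 15.47 − 21.70 = −6.23
- Full: −6.23 + (4 − 8) = −10.23

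| At-work loss, control to WORKWELL | Absence days, control to WORKWELL | Presenteeism only | Full | Effect of omission |
|---|---|---|---|---|
| 10% to 7% | 8 to 8 | −6.5 | −6.5 | none |
| 10% to 7% | 8 to 4 | −6.2 | −10.2 | saving understated |
| 10% to 7% | 8 to 12 | −6.8 | −2.8 | saving overstated |
| 10% to 7% | 8 to 16 | −7.1 | +0.9 | sign changes |
| 10% to 10% | 8 to 4 | +0.4 | −3.6 | sign changes |

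If the loss were instead applied to all scheduled days, the first four rows would all give (0.07 − 0.10) × 225 = −6.75. The last row would give 0, so the absence saving would be missed altogether.

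**When the sign changes.** Absence must move against the presenteeism component and by more than it. There are two routes:
- *Presenteeism improves and absence worsens.* The break-even rise in absence is (p0 − p1) × (W − A0) / (1 − p1).
  - 10% to 7%: 6.51 / 0.93 = 7.0 days
  - 10% to 5%: 10.85 / 0.95 = 11.4 days
  - 20% to 15%: 10.85 / 0.85 = 12.8 days
- *Absence falls and at-work loss does not.* With loss at 10% in both arms and absence falling from 8 to 4:
  - Presenteeism only: 0.10 × 221 − 0.10 × 217 = 22.1 − 21.7 = +0.4
  - Full: 26.1 − 29.7 = −3.6

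**The case against.** The strongest reply is that this is a condensed article. Nothing in it excludes absence, the employers' cost is not itemised, and the section Dissemination and author eligibility promises the full protocol. A WLQ-25 score needs a stated method to become money, whereas absence is already recorded in days, so naming one need not exclude the other. The section Outcomes also says presenteeism has the greatest impact on costs. And these are additional scenarios, while absenteeism will be reported as a secondary outcome in any case.

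Much of this stands, and it limits the point in three ways.
- A reader might infer that a day off sick is priced at zero. The document does not say so; that would be read from silence.
- A reader might infer that anyone without a WLQ-25 enters with no production loss. Sample size treats non-completion as attrition, and Data collection methods records unobtainable data as missing. A missing score is not a zero cost. The text also refers to long-term sick leave, so it does not follow that people with short absences lack a score.
- A reader might infer that the employer result will point the wrong way. That needs one of the two conditions shown in the working. The Background does report that a brief vocational rehabilitation trial in the USA reduced job loss but not presenteeism. That concerns job loss, not sick days, and gives no figure for this calculation.

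The reply does not dispose of the point. The article names which loss is converted and by which method, and it confines even the WPAI, which records time off, to presenteeism. That presenteeism is the larger cost supports its choice as primary outcome; it is no reason to leave absence out of an employer cost.

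**Conclusion.** The point holds for one analysis: the employer scenario using the human capital approach. Followed as written, it omits absence and will usually misstate the size of the employer-cost difference when the arms differ in absence. With equal absence in both arms the omission does no harm. With absence four days lower under WORKWELL, the illustration misses 4 of 10.2 day-equivalents of saving; with absence four days higher, it shows a saving of 6.8 instead of 2.8.

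A change of sign is possible, but only if absence rises by about 7 to 13 days per person-year against a presenteeism gain, or if absence falls while at-work loss stays about the same. All these sizes rest on assumed inputs, and the document gives no figure that shows a reversal.

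The NHS base case and the scenarios that use presenteeism as the effect measure are not affected in this way.

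**What to change.** In the human capital employer scenario:
- value the monthly recorded sickness-absence days at the same wage rate as presenteeism;
- apply the WLQ-25 loss only to time actually worked, so that no day is counted twice;
- show the absence and presenteeism components separately as well as their sum.

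The monthly records suit this better than the WPAI, which covers only the last seven days, and they can be valued for a participant on long-term sick leave who has no WLQ-25. If absence is deliberately left out, label the scenario as presenteeism cost only.

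The cost is analysis work; no new data collection is needed. The downside is that absence days are skewed and will widen the interval around employer costs.
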